### Control group

Patients in practices allocated to the control arm will continue to receive care as usual. In most practices, this will mean patients are recalled to different clinics to see different practice nurses to review each of their long-term conditions. The nurses will usually follow disease-specific computerised protocols for their management, and will mainly focus on collecting data related to QOF targets rather than quality of life or patients' priorities. The nature of ‘care as usual’ may vary between practices and over time—this will be explored in the process evaluation.

### Participant withdrawal

Among intervention practices, if any participant later requests not to receive the 3D intervention, they will revert to the usual care provided for other patients in their practice. Unless a patient requests to withdraw from the trial they will continue to be followed up and will be analysed in the group to which the practice was allocated. If they wish to withdraw from the trial, then no further follow-up data will be requested but data already provided will be used.

### Outcome measures

#### Primary outcome measures

The primary outcome for patient and carers will be health-related quality of life (HRQoL) as measured by the EQ-5D-5L after 15 months following patient recruitment.^31^ The EQ-5D is a widely used self-reported generic measure of HRQoL which has been validated in many different patient populations including diabetes, cardiovascular problems, chronic obstructive pulmonary disease, cancer, chronic pain and rheumatoid arthritis. The five-level version (EQ-5D-5L) contains the same dimensions as the earlier three-level version (EQ-5D-3L) but has been designed to provide greater reliability and sensitivity.

#### Secondary outcomes

Secondary outcome measures for participants are grouped under domains as shown in box 2.
Box 2Secondary outcomes for patients participating in the 3D trial*Experience of holistic patient-centred care*
Consultation and Relational Empathy (CARE) measure of relational continuity in general practitioner and nurse* consulations^32^Coordination of care (two questions from LTC6 Quality Innovation Productivity and Prevention (QIPP) programme)Patient Assessment of Chronic Illness Care (PACIC) measure^33^Overall satisfaction (single item)*Burden of illness measures*
Self-rated healthIllness burden in multimorbidity (Bayliss)^34^Quality of disease management (a composite measure of Quality and Outcomes Framework (QOF) achievement)^35^Hospital Anxiety Depression Scale (HADS)^36^*Burden of treatment*
Brief Treatment Burden Questionnaire†Morisky Medication Adherence Scale (eight-item)^37^Number of prescribed drugsNumber of high-risk drug combinations^38^*Not collected at 9 months follow-up†New measure developed for this study, based on qualitative interviews, item generation, principle components analysis and testing of psychometric properties.

Secondary outcome measures for carers will assess measures of carer quality of life and strain, including the EQ-5D-5L,^31^ the Carer Experience Scale^39^ and the Brief Treatment Burden Questionnaire for carers. These will be reported separately, as they are not participant outcomes.

#### Measures of process of care

We will monitor processes in the intervention practices in order to report the degree of implementation of the intervention. This will include the number of nurse and GP 3D reviews undertaken, the extent to which the 3D template was fully completed, the number of pharmacy reviews performed, whether an agenda and health plan were created and printed off to give to the patient, and the number of times the hospital general physician was contacted.

The continuity of care (COC) measure^40^ will be used as a measure of longitudinal continuity, for all telephone or face-to-face consultations by participants with GPs or nurses within the practice over the 15-month follow-up period, adjusted for continuity in the 15 months before the intervention.

Although also required for the economic analysis, the number of primary care consultations and the number of hospital admissions will be of particular interest as indicators of the effect of the intervention on primary and secondary health services.

We will report descriptively the systems in place to provide care for patients with multimorbidity in practices in both arms of the trial at baseline and at the end of the 15-month follow-up period, in particular to capture whether there are differences in ‘usual care’ in the control arm practices over the period of this study.

### Economic evaluation

The economic evaluation will be undertaken from the perspectives of (1) NHS and personal social services (PSS) and (2) patients. We will compare the extra cost of caring for patients in the intervention group with the difference in outcome as measured by the EQ-5D-5L and related quality-adjusted life years (QALYs). Resource use data will be collected from patient self-reported postal questionnaires at baseline, 9 and 15 months and GP practice records. The questionnaires will ask about the use of community and secondary care health services, social services, informal care, and personal costs (including travel, loss of earnings and dependent care costs). Patients indicating use of hospital services will be contacted by telephone to obtain more detail about the inpatient stay or accident and emergency visit. GP practice records will be used to obtain information about all available primary care contacts, including type of consultation and who was seen, tests and investigations, and prescribed medication.

Trial records will be used to estimate the cost of setting up the 3D service and training staff. This will be identified and reported separately from the running costs.

NHS resources will be valued using national published sources such as Curtis,^41^ NHS reference costs^42^ and the British National Formulary (BNF).^43^

### Data collection

At baseline, data will be collected on the sociodemographic measures (number of long-term conditions; age; gender; education; ethnicity; deprivation status (index of multiple deprivation based on postcode); work status) and all primary and secondary outcomes. The primary outcome will be collected 9 and 15 months after recruitment, with the primary outcome time point being at 15 months. All but one of the secondary outcomes will be collected at 9 months, as shown in box 2. All secondary outcomes, measures of the process of care and measures of resource utilisation will be collected 15 months after recruitment. Practice randomisation occurs after patient recruitment, and it then takes approximately 3 months to train practices to deliver the 3D intervention. Patients have their 3D reviews on a six-monthly cycle. Therefore, collecting outcome data 9 and 15 months after patient recruitment allows for a 3-month lag time and ensures that most patients will be invited to have two 3D reviews before outcomes are measured.

The primary method of self-reported data collection will be via postal questionnaires; however, alternative completion methods including by telephone or via a home visit by a researcher masked to treatment allocation will be offered if necessary in order to maximise response rates.

Two reminders, the first by letter or email (approximately 10–14 days after posting the questionnaire) and the second by phone (approximately 10–14 days after the first reminder), will be made for participants who have not returned their questionnaire. Patients will be given £5 gift vouchers for completion of questionnaires.

No data about identifiable patients will leave the practice unless patients have provided consent. All data will be stored securely and confidentially at the University of Bristol in line with its data management policies.

### Sample size

The study is designed to detect an effect size of 0.274 SDs in the primary outcome of the EQ-5D-5L. Data about the variability of the new five-level (5L) version of the EQ-5D is currently more limited than for the well-established three-level (3L) version. The SD of the EQ-5D-3L in the UK general population is 0.23, rising to 0.27 in the oldest respondents (aged over 75).^44^ Hence, an effect size of 0.274 would equate to a detectable difference of (0.274×0.27)=0.074 on the EQ-5D-3L, previously deemed to be the minimum important difference.^45^ Although there are less data about the variability in the 5L version of the EQ-5D than the 3L version, this latest version is likely to have greater sensitivity to change.^31^

Based on data available from our previous studies,^1^ we estimated that 2.3% of adult patients would have multimorbidity as defined in this study. This equates to about 108 patients in an average-sized practice of 6000 patients. Recruiting 32 practices would therefore provide 3456 potentially eligible patients. Assuming 40% of patients agree to participate (n=1382), 80% are followed up to 12 months, and an intraclass correlation coefficient (ICC) of 0.03 for clustering at the practice level (based on the WISE trial),^46^ 32 practices will provide approximately 90% power, with a 5% α level to detect an effect size of 0.274 SDs in the EQ-5D-5L measure between the intervention and control groups.

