**Methods and analysis:**

This is a pragmatic two-arm cluster randomised controlled trial. 32 general practices around Bristol, Greater Manchester and Glasgow will be randomised to receive either the ‘3D intervention’ or usual care. 3D is a complex intervention including components affecting practice organisation, the conduct of patient reviews, integration with secondary care and measures to promote change in practice organisation. Changes include improving continuity of care and replacing reviews of each disease with patient-centred reviews with a focus on patients' quality of life, mental health and polypharmacy. We aim to recruit 1383 patients who have 3 or more chronic conditions. This provides 90% power at 5% significance level to detect an effect size of 0.27 SDs in the primary outcome, which is health-related quality of life at 15 months using the EQ-5D-5L. Secondary outcome measures assess patient centredness, illness burden and treatment burden. The primary analysis will be a multilevel regression model adjusted for baseline, stratification/minimisation, clustering and important co-variables. Nested process evaluation will assess implementation, mechanisms of effectiveness and interaction of the intervention with local context. Economic analysis of cost-consequences and cost-effectiveness will be based on quality-adjusted life years.

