#### Patients

Inclusion criteria are being aged 18 years or over, being registered with a usual doctor who is participating in the research study and having three of more chronic conditions from those included in the National Health Service (NHS) Quality and Outcomes Framework^24^ (QOF, V.31.0)—see box 1.
Box 1Chronic conditions for inclusionIncluded patients have three or more diagnoses from the following groups of chronic conditions:
Cardiovascular disease or chronic kidney disease (including coronary heart disease, hypertension, heart failure, peripheral arterial disease, chronic kidney disease stage 3–5)*StrokeDiabetesChronic obstructive pulmonary disease or asthma*EpilepsyAtrial fibrillationSevere mental health problems (schizophrenia or psychotic illness)*DepressionDementiaLearning disabilityRheumatoid arthritis*Groups are counted only once even if a patient has multiple conditions within a group. For example, having both hypertension and heart failure would just count for one condition.

Exclusion criteria are: having a life expectancy of less than 12 months; serious suicidal risk; known to be leaving the practice within 12 months; unable to complete questionnaires in English even with the help of carers; actively taking part in other research involving extra visits to primary care or other health services; lacking capacity to consent (as coded in their practice records, or determined by their GPs, in Scotland only); being considered unsuitable for the research study by their GP (eg, recently bereaved or currently hospitalised).

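### The power calculation uses retention at 12 months for an outcome measured at 15 months, and its figure of about 90% also needs normal quantiles; with a t reference for 32 practices it is 87.5% at 80% retention

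*Protocol article*

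**What the plan says.** In the Sample size section the protocol expects 1382 participants from 32 practices and assumes that "80% are followed up to 12 months, and an intraclass correlation coefficient (ICC) of 0.03 for clustering at the practice level". It concludes that "32 practices will provide approximately 90% power, with a 5% α level to detect an effect size of 0.274 SDs". That effect is tied to a difference of 0.074 on the EQ-5D-3L, using an SD of 0.27, which the protocol describes as the minimum important difference. The abstract carries the claim forward: "This provides 90% power at 5% significance level to detect an effect size of 0.27 SDs in the primary outcome".

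The primary outcome is HRQoL "as measured by the EQ-5D-5L after 15 months following patient recruitment". The Data collection section confirms 15 months as the primary time point and schedules follow-up questionnaires at 9 and 15 months only. It also explains that about 3 months pass between recruitment and delivery of the intervention. Allocation is by practice, 1:1, so 16 practices per arm.

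The patient exclusions look 12 months ahead: life expectancy under 12 months, and "known to be leaving the practice within 12 months".

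**The concern.** The retention input belongs to a time at which the trial measures nothing, and no retention figure is given for 15 months. Loss to follow-up starts at recruitment, and the two exclusions that would reduce it reach only to month 12, so they do not screen out expected losses in months 12 to 15.

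Separately, the treatment contrast is between practices. With 16 per arm, a normal reference is slightly optimistic, and the power figure depends on it.

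There is no slack to absorb either point, because about 90% power is claimed exactly at the difference the protocol calls minimally important. If the true figure is lower, a null result would be read as somewhat stronger evidence against a difference of 0.074 than the design supports.

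**Working it through.** **Inputs from the protocol.** 1382 recruited; 32 practices; 80% retained; ICC 0.03; effect 0.274 SD; 5% alpha (sidedness is not stated; taken as two-sided); 1:1 allocation.

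**Formulae.** Analysed N = 1382 × retention; m = N/32. Design effect DE = 1 + (m − 1) × 0.03. With unequal clusters, DE = 1 + ((1 + CV²)m − 1) × 0.03. Effective n per arm = N/(2 × DE). Noncentrality = 0.274/√(2/n). Power comes from the normal distribution, or from the noncentral t with 32 − 2 = 30 df.

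**The plan's own figure.** N = 1382 × 0.80 = 1105.6; m = 34.55; DE = 1 + 33.55 × 0.03 = 2.0065; n = 1105.6/(2 × 2.0065) = 275.5 per arm; noncentrality = 0.274/√(2/275.5) = 3.216. Power with normal quantiles is **89.5%**, so the stated figure reproduces. The same inputs with t(30) give **87.5%**. This step needs no assumption about month 15.

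**Retention at 15 months (assumed).** The protocol gives no value. Constant loss would turn 80% at 12 months into 0.80^(15/12) = 75.7%. I take 70% as a lower case.

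| Retention | N | DE | n per arm | Power, z | Power, t(30) |
|---|---|---|---|---|---|
| 80% | 1105.6 | 2.006 | 275.5 | 89.5% | 87.5% |
| 75.7% | 1045.6 | 1.950 | 268.1 | 88.7% | 86.6% |
| 70% | 967.4 | 1.877 | 257.7 | 87.5% | 85.3% |

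With z, the time point alone costs 0.8 points (constant loss) to 2.0 points (70%). At any given retention, moving from z to t(30) costs about 2 points.

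**Unequal clusters (assumed CV 0.3).** Practice lists have a minimum of 4500 and an assumed average of 6000, and at most 150 patients per practice are sampled, so cluster sizes will vary. The CV is not given. At 0.3, t(30) power is 86.0% at 80% retention, 85.1% at 75.7% and 83.8% at 70%, about 1.5 points lower in each case. With z at 80% retention it is 88.2%.

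**Effect detectable with 90% power, t(30), equal clusters.** 0.285 SD at 80% retention, 0.289 at 75.7% and 0.295 at 70%. Multiplied by 0.27 these are 0.077, 0.078 and 0.080, against the protocol's 0.074.

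**Baseline adjustment (assumed correlation r).** Scaling the variance by 1 − r² with r = 0.4, t(30) power is 92.4% at 80% retention, 91.7% at 75.7% and 90.7% at 70% with equal clusters. With CV 0.3 it is 91.3%, 90.6% and 89.5%.

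**The case against.** The strongest reply is that nothing here is an arithmetic error. The protocol claims about 90%, and its inputs give 89.5%. That is correct, and a reader should not infer that the calculation was done wrongly.

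Second, the time point costs little. At constant loss power is 88.7%, which could still be called about 90%. The 12 months might also be counted from the start of the intervention, given the 3-month lag, or 80% might be meant as the final follow-up rate. On either reading the mismatch costs nothing. This stands as a limit on the size of the point, but the Sample size section says neither, so the text still needs reconciling.

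Third, unequal clusters alone do not break the figure. With normal quantiles and a CV of 0.3, power is 88.2%, so it would be too strong to say that the stated power requires identical practice sizes.

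Fourth, the calculation takes no credit for baseline EQ-5D-5L, and a moderate correlation removes the shortfall. This also stands, but the protocol is not consistent on it: the abstract puts baseline in the primary model, while the Statistical methods section leaves it to subsequent models.

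A reader might also infer inflated type I error from testing a multilevel model with few clusters. The protocol does not specify the estimator or the reference distribution for the test. Those are details for the statistical analysis plan, and no finding is made on them.

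**Conclusion.** The point holds as a modest one. The retention assumption does not match the primary time point and is not explained. The stated power needs normal quantiles; a t reference for 32 practices gives 87.5% at 80% retention.

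A range of about 85–87% applies only if 15-month retention is roughly 70–76%, with t(30), equal clusters and no baseline adjustment. It is conditional on those assumptions and is not a figure the documents establish. Likewise, the statement that the effect detectable with 90% power exceeds 0.074 applies to the model without baseline. A reader might conclude that the trial is materially underpowered; the documents do not support that, because the separate losses are about 1 to 2 points each and baseline adjustment could offset them.

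**What to change.** In the Sample size section, state the retention assumed at 15 months after recruitment, or say explicitly that 80% applies at that time. Recompute power with a t reference on practice-level degrees of freedom and an allowance for unequal cluster sizes, giving the CV used. Restate the section and the abstract to match. With equal clusters this is about 87% at 80% retention, or about 85–87% at 70–76%, before any baseline adjustment; the CV allowance lowers these by about 1.5 points at CV 0.3.

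Settle whether baseline EQ-5D-5L is in the primary model. If it is, report the gain in power with the correlation assumed.

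The cost is one rewritten paragraph, one abstract figure and a slightly less favourable headline. Recruitment has closed and should not be extended on this account.

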### Allocation

General practices will be the unit of allocation. Practices will be allocated in a 1:1 ratio to receive either the intervention or continue care as usual (control group). Randomisation will be stratified by area (Bristol, Greater Manchester, Glasgow) and minimised by deprivation level and practice size. Within each area allocation will be performed in blocks of two, with both practices in a block randomised at the same time and released to the trial manager together to ensure allocation concealment and no selection bias. It was not deemed possible to increase or vary the block sizes given the small number of practices recruited to each area and the dynamic nature of recruitment. The trial manager will notify the local research team of the two allocations and they will then notify the practices and arrange training of the intervention practice. The allocation schedule will be computer-generated by the trial statistician, blind to details of the practices apart from those needed for stratification and minimisation.

Randomisation of a practice will take place after patients in that practice have been identified and invited to participate in order to avoid selection bias.

### Blinding

Once participants have been recruited, it will not be possible to mask participants or healthcare professionals to the group allocation of their practice. It is also not feasible to blind all members of the study team actively involved in the execution of the study. However, data entry and checks of data quality will be conducted by administrative staff masked to treatment allocation. Analysis of outcomes will be performed by the trial statistician, also masked to treatment allocation.

### Statistical methods

Data will be analysed in accordance with CONSORT principles and its extension for cluster randomised trials. Descriptive statistics will be used to summarise characteristics of practices and patients and compare baseline characteristics between groups. A full statistical analysis plan will be developed and agreed by the Data Monitoring Committee (DMC) and the Trial Steering Committee (TSC) after completion of the pilot phase and prior to undertaking any analyses of the main trial.

All analyses of primary and secondary outcomes will be at the patient level and will account for clustering by practice using multilevel regression models. Analyses will be performed on an ‘as allocated’ basis. Primary analysis comparing EQ-5D-5L between the intervention and control practices will employ a linear multilevel regression model adjusted for stratification/minimisation variables. Subsequent models will adjust for baseline EQ-5D-5L, any variables demonstrating imbalance at baseline and other important prognostic variables such as age, number of long-term conditions, deprivation and depression. Preplanned analyses of secondary outcomes will also employ linear or logistic (as appropriate) multilevel regression models.

Formal tests of interaction will be performed to consider the following potential effect modifiers: age, number of chronic conditions, index of deprivation, and presence or absence of depression alongside physical health problems. The trial is not specifically powered for such interaction tests; hence, interpretation will focus on the CIs and will be hypothesis-generating only. The potential impact of missing data will be examined through sensitivity analyses.

Anonymised data will be used in order to compare descriptive data for consenting versus non-consenting patients. We will explore the possibility of comparing QOF performance in patients with chronic conditions both with and without multimorbidity—this is to assess for the potential unintended consequence that concentrating effort on patients with multimorbidity may have a positive or negative impact on the care of other patients.

No interim analyses are planned.

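### The Abstract and the Statistical methods section give different covariate sets for the primary analysis, and the Statistical methods version leaves baseline EQ-5D-5L out

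*Protocol article*

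**What the plan says.** The Abstract (Methods and analysis) states: "The primary analysis will be a multilevel regression model adjusted for baseline, stratification/minimisation, clustering and important co-variables".

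The Statistical methods section states that the primary comparison of EQ-5D-5L "will employ a linear multilevel regression model adjusted for stratification/minimisation variables. Subsequent models will adjust for baseline EQ-5D-5L". The second of these sentences lists what is deferred: "Subsequent models will adjust for baseline EQ-5D-5L, any variables demonstrating imbalance at baseline and other important prognostic variables", giving age, number of long-term conditions, deprivation and depression as examples.

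The Allocation section defines the design variables: "Randomisation will be stratified by area (Bristol, Greater Manchester, Glasgow) and minimised by deprivation level and practice size". Baseline EQ-5D-5L is not among them, so it does not enter the Statistical methods model by that route.

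The baseline value is planned to be available. The list of baseline data under Data collection ends with "work status) and all primary and secondary outcomes".

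The Statistical methods section also says that a full SAP is to be agreed with the two oversight committees before any main-trial analysis.

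**The concern.** There is one primary outcome at one time point, and two covariate sets are attached to the analysis called primary. The estimate, its confidence interval and its p value depend on which description is followed. Authors of the SAP inherit two conflicting public statements, and either choice can later be read as a change to the published primary analysis.

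The more detailed section also holds the less efficient version. The baseline value of an outcome is usually among its best predictors, and here it costs nothing extra to use. Only 32 units are randomised, and neither stratification nor minimisation acts on baseline EQ-5D-5L. The arms can therefore differ on it by chance, and a model without it makes no correction for that difference.

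The adjusted alternative is not fully fixed either. The Abstract does not name its additional covariates, and the Statistical methods section would choose some by the imbalance observed.

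**Working it through.** **1. The two descriptions compared**

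| Element | Abstract | Statistical methods |
|---|---|---|
| Practice clustering | in | in |
| Area, practice deprivation level, practice size | in | in |
| Baseline EQ-5D-5L | in | subsequent models |
| Other prognostic covariates | in, not named | subsequent models, examples given |
| Variables imbalanced at baseline | not mentioned | subsequent models |

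The entries for baseline EQ-5D-5L and other prognostic covariates cannot both describe the primary model.

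**2. Reproducing the planned power**

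Inputs from the Sample size section: 1382 recruited, 80% followed up, 32 practices, ICC 0.03, 5% α (taken as two-sided), effect 0.274 SD. Allocation is 1:1.

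- Analysed: 1382 × 0.80 = 1105.6
- Mean cluster size: 1105.6 / 32 = 34.55
- Design effect: 1 + (34.55 − 1) × 0.03 = 2.006
- Effective N: 1105.6 / 2.006 ≈ 551
- SE of the difference: √(4 / 551) = 0.0852 SD
- Power: Φ(0.274 / 0.0852 − 1.96) = 89.5%

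This agrees with the stated figure of about 90%. A t reference on 30 degrees of freedom gives 87.5%. The calculation has no baseline term, so it corresponds to the model in the Statistical methods section.

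**3. Adding baseline EQ-5D-5L**

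Let r be the baseline to 15-month correlation. The article does not give it, so r is an assumption, taken to be the same at patient and practice level. Then SE(adjusted) = 0.0852 × √(1 − r²). The difference detectable at 90% power is (1.96 + 1.282) × SE. The last column multiplies that by the SD of 0.27 that the article itself uses ("an effect size of 0.274 would equate to a detectable difference of (0.274×0.27)=0.074 on the EQ-5D-3L").

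| r (assumed) | SE (SD units) | SE reduction | Power at 0.274 SD | Detectable, SD | Detectable, EQ-5D points |
|---|---|---|---|---|---|
| no baseline | 0.0852 | – | 89.5% | 0.276 | 0.075 |
| 0.3 | 0.0813 | 5% | 92.1% | 0.263 | 0.071 |
| 0.5 | 0.0738 | 13% | 96.0% | 0.239 | 0.065 |
| 0.6 | 0.0682 | 20% | 98.0% | 0.221 | 0.060 |
| 0.7 | 0.0608 | 29% | 99.4% | 0.197 | 0.053 |

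The 95% confidence interval half-width is 0.167 SD without baseline, 0.145 SD at r = 0.5 and 0.119 SD at r = 0.7.

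**4. How far chance imbalance carries over**

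With equal SDs at the two times, a baseline difference between arms shifts the estimate without baseline by about r times that difference. If baseline EQ-5D-5L has the same SD and ICC as the outcome, one standard error of baseline imbalance is about 0.085 SD. The resulting shift is 0.5 × 0.085 = 0.043 SD at r = 0.5, or 0.7 × 0.085 = 0.060 SD at r = 0.7. Adjustment for area, deprivation level and practice size may reduce this somewhat.

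**The case against.** The strongest reply is that the Statistical methods model is a legitimate choice. Randomisation makes it valid, and its confidence interval already allows for chance imbalance. The sample size was planned on it, and baseline adjustment is still planned in later models. The Abstract may simply have compressed a sequence of models into one sentence. A SAP agreed before analysis, a statistician masked to allocation and no interim analyses together give a clear point at which one model can be fixed.

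Most of this stands, and it rules out several stronger readings that a reader might infer:

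- **That the trial is underpowered.** The planned power is met without baseline. What is lost is efficiency.
- **That the analyst will have two primary results to choose from.** If the choice stayed open until results were seen, the chance that at least one model reached two-sided 5% under the null would be about 7.3% at r = 0.5 and 8.3% at r = 0.7, taking the correlation of the two estimates as √(1 − r²). The planned SAP step can close that route, so the article does not establish any such inflation.
- **That a baseline difference passes in full into the estimate.** It carries over only in proportion to the association between baseline and follow-up, and the model does adjust for the three design variables.
- **That every participant has a baseline value obtained before randomisation.** Data collection says that these data will be collected and that randomisation follows recruitment. Allocation ties randomisation to patients having been identified and invited. Neither section promises completeness or that every form comes before allocation.

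The reply does not remove the disagreement between two sections on what the primary model contains. Compression may explain it, but the Abstract's sentence assigns those covariates to the primary analysis. This is not detail left to the SAP, because the article states the covariate set twice and differently.

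**Conclusion.** The contradiction is real and concerns the headline analysis, so it should be settled before any analysis. The case rests on the conflicting descriptions, with precision as a supporting reason to prefer the model that includes baseline.

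The size of the gain depends on an r that the article does not supply. It is modest at 0.3 and substantial at 0.6 or 0.7. The direction, a smaller standard error, holds for any appreciable correlation. The figures also assume equal explained variance at both levels and the article's own ICC, follow-up rate and SD. They do not show bias or inadequate power in the Statistical methods version.

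**What to change.** Edit both the Abstract and the Statistical methods section, and carry the same text into the SAP before any analysis:

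- Name one primary model: a linear multilevel model for 15-month EQ-5D-5L with a practice random intercept, adjusted for baseline EQ-5D-5L, area, practice deprivation level and practice size.
- Either list the Abstract's additional covariates by name in advance or remove them from the primary model. Changing the Statistical methods section alone would leave the two descriptions in conflict.
- Do not select primary-model covariates by observed baseline imbalance.
- State a simple rule for missing baseline EQ-5D-5L, such as mean imputation or a missing-value indicator.
- Label the model without baseline a sensitivity analysis.

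The cost is a few sentences. No new data and no change to the sample size are needed. The sponsor should also confirm whether baseline forms are completed before each practice is allocated.
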